## 5. Study design

### *5.1 Design*

This study will use a stepped-wedge cluster randomized trial to evaluate a health system initiative. Oncology practices will be randomly assigned in sequential four-week blocks to receive the email prompt intervention, in which individual oncologists will receive an automated weekly email detailing 1) how many serious illness conversations they have had, 2) how their number of serious illness conversations compares to peer oncology providers across UPHS, and 3) a weekly roster of their upcoming patients at high risk of short-term mortality as determined by our mortality prediction algorithm (see below), viewable on a HIPAA-compliant secure web interface. Clinicians will receive a HIPAA compliant text message on the morning of the appointment reminding them to consider a serious illness conversation with patients on the list. Providers may opt out of this reminder on the web interface containing the weekly patient roster of high risk patients. Prior to receiving the intervention, practices will receive current standard communications regarding serious illness performance until they are randomized to the intervention. Practices will be cluster-randomized to the intervention over a 16-week period, after which all practice physicians will receive the email intervention.

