### *5.2 Study duration*

The study is expected to begin in June 2019 and take 10 months (16 weeks for intervention + 24 weeks followup) to complete.

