### *5.4 Accrual*

Patients will accrue to the trial as their clinical practice receives the email intervention. Eight University of Pennsylvania oncology practices will be randomly assigned to one of four start dates separated by four weeks, resulting in four pairs of clinics starting the intervention two clinics at a time every four weeks over sixteen weeks. When a clinic reaches the assigned start date for the intervention arm, the clinicians will begin to receive the weekly email intervention and text reminders. Based on previous studies and assuming a baseline SIC rate of 0.65 SICs per

provider per 4-weeks, we believe we will have over 80% power to detect a 60% increase in SIC rates per provider per 4-weeks.

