### 8.2 Procedures

Data on oncologists and their patients at the University of Pennsylvania Health System will be obtained from Penn Data Store and Clarity (Epic's data reporting database). Physician data includes demographic information (e.g. sex, type of medical degree, etc.) and may be also obtained from publicly available databases or websites online. The predictive algorithm identifies high-risk patients based on demographic information, information about comorbid conditions (including type of cancer; other variables like diabetes, hypertension, and chronic kidney disease, and comorbid conditions needed to calculate the Charleston Comorbidity Index; laboratory test results; and previous emergency department and hospital admissions. This predictive algorithm has been validated and results are currently being submitted for publication in a medical journal. Clarity will be used to identify documentation of SICs and ACP.

After identifying eligible oncologists, block randomization will occur at the clinic level (noting that PCAM melanoma and CNS Oncology will be randomized together as both clinics have a low number of providers). We will obtain baseline measures and plan to stratify the randomization by those above and below median level of SICPs in March through May of 2019.

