## 9. Analysis plan

All analyses will be conducted using intention-to-treat using the patient as the unit of analysis and clustering at the level of the oncologist. Advanced practice providers (APPs) will receive the intervention, but will be associated with the oncologist with whom they work for the purposes of the analysis. All hypothesis tests will use a two-sided alpha of 0.05 as our threshold for statistical significance.

The primary and secondary outcome measures will use a binary indicator representing the presences of an SIC or ACP for each patient. The primary outcome will be expressed as a standardized rate of documented SIC discussions (number of documented SIC notes / 100 unique patient visits). In the main adjusted analysis, we will fit models using generalized estimating equations cluster on oncologists, using group (oncology practices) and period (4-week increments) fixed effects and adjusting for monthly temporal trends.

To test the robustness of our findings, we will perform sensitivity analyses that adjusts for available patient characteristics and comorbidities such as demographics and the Charlson Comorbidity Index.

Additional sensitivity analyses will include:

- Including patients enrolled in aforementioned palliative care lung cancer trial
- Analyzing results clustering at the level of the clinician (oncologist or APP)

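### The main model assumes an effect that is constant from the first four weeks of exposure; if the nudge builds or fades, its single coefficient mainly reflects the first exposure block and can miss the average effect delivered by a wide margin

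*Protocol*

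**What the plan says.** Section 9 (Analysis plan) of the Protocol bases the main adjusted analysis on GEE with the oncologist as the cluster. The terms of the model are given as "using group (oncology practices) and period (4-week increments) fixed effects and adjusting for monthly temporal trends". The threshold is a two-sided 0.05. The sensitivity analyses listed there cover patient characteristics and comorbidities, inclusion of patients from the palliative care lung cancer trial, and clustering by clinician. None concerns time since a practice started.

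On the schedule, section 5.4 (Accrual) says "Eight University of Pennsylvania oncology practices will be randomly assigned to one of four start dates separated by four weeks", two practices at a time. Section 5.1 (Design) adds: "Practices will be cluster-randomized to the intervention over a 16-week period, after which all practice physicians will receive the email intervention". Section 5.2 (Study duration) gives the length: "take 10 months (16 weeks for intervention + 24 weeks followup) to complete". Section 8.2 (Procedures) mentions a baseline window, for stratification: "stratify the randomization by those above and below median level of SICPs in March through May of 2019". The Protocol does not say whether the baseline or the follow-up weeks enter the main model.

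The intervention is repeated: "individual oncologists will receive an automated weekly email detailing 1) how many serious illness conversations they have had", together with a peer comparison, a roster of high-risk patients, and a text on the day of the visit that providers may opt out of (section 5.1).

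**The concern.** Both time terms in the main model are calendar time. Neither describes how long a practice has been exposed. A single intervention coefficient then assumes that the effect reaches its final size in the first four weeks and stays there. Weekly feedback with peer comparison could plausibly accumulate, and reminders could plausibly be ignored or switched off.

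In a stepped-wedge design with practice and period effects, practices that have already started serve as comparators for those that start later. If the effect changes with exposure, the single coefficient is a weighted sum of the block-specific effects, and some of the weights are negative. The estimate can then lie well below or well above the average effect delivered. The listed sensitivity analyses would not reveal this.

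**Working it through.** **Inputs.** Eight practices, four start dates four weeks apart, two practices per date (5.4); 16-week roll-out (5.1); 24 weeks of follow-up, or six 4-week periods (5.2); March to May 2019 taken as three 4-week baseline periods (8.2). Assumptions: one treatment term, equal cell sizes, linear scale. Because the Protocol leaves the included periods open, 0, 1 and 3 baseline periods were tried, each with and without follow-up. The Protocol's power figure (section 5.4) cannot be reproduced, since no number of oncologists or correlation is given, and this point does not use it.

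**Formula.** Let D(s,t) = 1 if start group s is exposed in period t. After removing practice and period effects, R(s,t) = D(s,t) − row mean − column mean + overall mean. The weight on exposure block k is w(k) = [sum of R over cells in block k] / [sum of R × D over all cells]. The estimate is the sum of w(k) × effect(k).

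**Worked case: three baseline periods plus 16 weeks.** Row means are 4/7, 3/7, 2/7, 1/7. Column means are 0, 0, 0, 0.25, 0.50, 0.75, 1. The overall mean is 10/28 = 0.357.

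- Block 1: 0.536 + 0.429 + 0.321 + 0.214 = 1.500
- Block 2: 0.286 + 0.179 + 0.071 = 0.536
- Block 3: 0.036 − 0.071 = −0.036
- Block 4: −0.214
- Denominator: 1.500 + 0.536 − 0.036 − 0.214 = 1.786

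Dividing gives weights 0.84, 0.30, −0.02, −0.12.

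**Weights in all six layouts.**

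| Baseline periods | Follow-up | Block 1 | Block 2 | Block 3 | Block 4 onward |
|---|---|---|---|---|---|
| 0 | no | 1.20 | 0.30 | −0.20 | −0.30 |
| 1 | no | 1.00 | 0.30 | −0.10 | −0.20 |
| 3 | no | 0.84 | 0.30 | −0.02 | −0.12 |
| 0 | yes | 0.75 | 0.375 | 0.125 | four zeros, −0.075, −0.10, −0.075 |
| 1 | yes | 0.73 | 0.37 | 0.12 | four zeros, −0.07, −0.09, −0.07 |
| 3 | yes | 0.71 | 0.355 | 0.118 | four zeros, −0.055, −0.073, −0.055 |

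**Two illustrative shapes, three baseline periods plus 16 weeks.** Blocks 1 to 4 contain 4, 3, 2 and 1 start groups, so the delivered average is weighted 4:3:2:1.

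- Linear build-up (0.25, 0.50, 0.75, 1): estimate 0.84×0.25 + 0.30×0.50 − 0.02×0.75 − 0.12×1 = 0.225. Delivered average (4×0.25 + 3×0.50 + 2×0.75 + 1×1)/10 = 0.50.
- Halving every 8 weeks (1, 0.707, 0.5, 0.354): estimate 0.840 + 0.212 − 0.010 − 0.042 = 1.00. Delivered average (4 + 2.121 + 1 + 0.354)/10 = 0.75.

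**Same shapes with follow-up added.** There are now 34 exposed start-group cells. For the build-up, held at full size after block 4, the estimate is 0.26 and the delivered average is (4×1.5 + 22)/34 = 0.82. For halving, the estimate is 1.01 and the delivered average 0.38.

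**Other layouts.** Linear build-up over 16 weeks gives 0.125 with one baseline period. With none it gives 1.20×0.25 + 0.30×0.50 − 0.20×0.75 − 0.30×1 = 0.00.

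**Checks.** The weights checked by GLS did not change under exchangeable within-oncologist correlation of 0, 0.1 or 0.5. On the logit scale, with an assumed 2% baseline and a long-run odds ratio of 1.6, the build-up with three baseline periods gave 1.10 (1.09 with unequal group sizes). A constant effect was recovered as 1.60.

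**The trend clause.** Adding a linear trend to practice and period effects adds a column but no rank (rank 8 of 9 columns in the layout with one baseline period and 16 weeks), so it is exactly aliased. Calendar-month indicators left the logit estimates unchanged to three decimals.

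**The case against.** Practice plus period fixed effects is a standard stepped-wedge model, the treatment term is not written out, and a statistical analysis plan that is not shown could add an exposure-time analysis. That is fair: the single effect is an inference, though the natural one, and the main model itself is already fixed in section 9.

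The shapes are assumed. Nothing in the Protocol predicts a 16-week build-up, and the roster and same-day text act at the visit. If the effect is half size in block 1 and full afterwards, the layouts with a baseline period give 0.50 to 0.65 of full, against delivered averages of 0.80 to 0.94. The shortfall is smaller but does not vanish.

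Three stronger readings are tempting, and the documents support none of them.

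- **A real effect would be estimated as zero.** For the 16-week build-up this needs a model with no baseline period. That sits badly with section 5.6, which requires providers to have enough high-risk patients before the intervention (the first two practices would have no such period), and with section 8.2, which plans baseline measures. Some other shapes also reach zero, for example no effect in block 1 and full effect after it with one baseline period (0.30 − 0.10 − 0.20 = 0.00). So zero is a possibility for particular combinations of shape and periods, not the expected result.
- **Adjusting twice for calendar time causes the distortion.** It does not. The second adjustment is redundant and leaves the estimates as they were.
- **False positives are inflated.** If there is no effect at any exposure time, the estimate is centred on zero.

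**Conclusion.** The point stands as a weakness of the constant-effect assumption. In every layout tried, the first four weeks of exposure carry 0.71 to 1.20 of the weight, block 2 carries 0.30 to 0.375, and exposure beyond block 3 carries zero or negative weight. With three baseline periods, a 16-week build-up is estimated at less than half of its delivered average without follow-up (0.23 against 0.50) and about a third with it (0.26 against 0.82). A fading effect is overstated (1.00 against 0.75, or 1.01 against 0.38).

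These figures rest on one treatment coefficient, equal cells, a linear scale and the stated shapes. If the effect is constant from the start, or absent, the model is unbiased and nothing is lost. The trend clause is a separate matter of tidiness.

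**What to change.** In section 9:

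1. Delete the clause on monthly temporal trends and keep the practice and 4-week period effects.
2. State which periods enter the model, and include the March to May 2019 baseline periods.
3. Keep the constant-effect estimate as the primary test.
4. Pre-specify one supporting model with a separate effect for each 4-week block since start. Report the block effects and their average over a range fixed in advance, for example the first three blocks, beside the primary estimate.
5. State that, if the block effects are not flat, the primary estimate will be read as mainly an early-exposure effect. Do not add a rule that moves the primary conclusion to the other model after seeing the data: that would give two routes to significance under a single 0.05.

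Cost: one extra model on data already collected, with a wider interval. With equal, independent cells and eight practices, the variance of the three-block average against that of the constant effect is 0.398 against 0.280 with three baseline periods, so the standard error is √(0.398/0.280) = 1.19 times as large. The ratio is 1.29 if follow-up is also included. Without baseline it is √(1.413/0.400) = 1.88, or 2.31 with follow-up, which is a further reason to include the baseline. A three-block average describes only the first 12 weeks of exposure: under the build-up above it would be (0.25 + 0.50 + 0.75)/3 = 0.50 of the full effect, so the individual block effects should be shown with it.

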## **11. Human research protection**

### *11.1 Data confidentiality*

Computer-based files will only be made available to personnel involved in the study through the use of access privileges and passwords. Wherever feasible, identifiers will be removed from study-related information. Precautions are already in place to ensure the data are secure by using passwords and HIPAA-compliant encryption.

### *11.2 Subject confidentiality*

Data on physicians and patients will be obtained from Epic, Penn Data Store and Tableau. Any information that is obtained will be used only for research purposes and to inform the behavioral nudges described above. Information on individual patients will only be disclosed within the study team. All study staff will be reminded of the confidential nature of the data collected and contained in these databases.

Data regarding provider performance of Serious Illness Conversations are already shared among providers and will continue to be shared in unblinded fashion as part of the trial. Data regarding acute care utilization in the last 30 days for a provider's deceased patient panel will be shared amongst providers as well. This will occur as part of the intervention but is planned to occur occur regardless of trial approval as part of quality improvement efforts.

Data will be stored, managed, and analyzed on a secure, encrypted server behind the University of Pennsylvania Health System (UPHS) firewall. The primary investigator ([name]) and statistical analyst will be blinded to the randomization schema and which groups are receiving the intervention. This server was created for projects conducted by the Penn Medicine Nudge Unit related to physician and patient behavior at UPHS. All study personnel that will use this data are listed on the IRB application and have completed training in HIPAA standards and the CITI human subjects research. Data access will be password protected. Whenever possible, data will be deidentified for analysis.

### *11.3 Subject privacy*

All efforts will be made by study staff to ensure subject privacy. Data will be evaluated in a de-identified manner whenever possible.

### *11.4 Data disclosure*

Information on physicians and patients will not be disclosed to anyone outside of the study team, with the exception of provider level data (SIC rates, acute care utilization) that are deliberately shared as a part of the behavioral nudges.

### *11.5 Data safety and monitoring*

The investigators will provide oversight for the study evaluation of this health system initiative. Providers will use their clinical judgment to determine the appropriateness of initiating ACPs with patients, in accordance with standard of care.

### *11.6 Risk/benefit*

#### *11.6.1 Potential study risks*

The potential risks associated with this study are minimal. Breach of data is a potential risk that will be mitigated by using HIPAA compliant and secure data platforms for the nudge interventions (name of list platform and platform used to share info w/ MAs) and evaluation (Nudge Unit server). As noted above, substantial data demonstrates that ACPs improve patient goal-concordant care without any identified harms (despite concerns that ACPs may increase psychosocial distress, the opposite has been found), so the negative impact on patients is minimal.

The provider data that will be shared with providers is already shared in one form (in the case of SIC rates) and is planned to be shared with providers in the near future independent of this trial (in the case of acute care utilization near the end of life), so the trial does not expose providers to additional risk.

#### *11.6.2 Potential study benefits*

As described in the literature, patients may have improved quality of life and better goal-concordant care when exposed to ACPs, especially earlier in their disease course. An intervention that prompts providers to have an ACP with patients at a high risk of death in the next six months may increase the likelihood that these conversations occur and that they occur earlier in the disease course. However, it is possible that patients will receive no benefit from this study.

#### *11.6.3 Risk/benefit assessment*

The risk/benefit ratio is highly favorable given the potential benefit from eligible patients having an SIC or ACP discussion with their provider and benefitting from better goal-concordant care and that efforts have been put into place to minimize the risk of breach of data.
